### Sample size calculations

A sample of 182 (91 per arm) is necessary to detect a minimum important difference of 1.2 sessions in the adherence primary outcome (number of days strengthening exercises performed in previous fortnight) at 26 weeks between groups (based on data from our trial evaluating SMS behaviour change messages [27]) with 80% power and an alpha of 0.025 (alpha of 0.05 split between the two primary outcomes), assuming a between-participant SD of 2.4 [27] and 15% attrition [28]. This sample size ensures more than 80% power to detect the minimal important difference on the clinical primary outcome of 6 units in change (follow-up minus baseline) in physical function on WOMAC [55] between the two arms, assuming a between-participant SD of 12 units [28], a baseline to 26-week correlation of 0.5 [28], an alpha of 0.025 and 15% attrition [28]. Physiotherapists treat participants in both groups, thus we have not modified the sample size for physiotherapist clustering.

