**Methods:**

This is a two-arm, pragmatic, superiority randomised trial. One hundred and eighty two Australians with chronic knee pain (clinical knee OA) and who have at least a mild level of physical dysfunction are being recruited. Participants are randomly allocated i) exercise (physiotherapist-prescribed exercise) or; ii) exercise plus app (physiotherapist-prescribed exercise plus access to the ‘My Exercise Messages’ mobile app). Exercise care comprises two videoconferencing consultations with a physiotherapist over two weeks (30 min each) for a strengthening exercise program, which is then conducted independently at home for 24 weeks without any further physiotherapist consultations. Participants are also provided with exercise resources to facilitate home-based exercise. Those randomised to exercise plus app will download the app after completing the two weeks of physiotherapy consultations and will be instructed by research staff to use the app for the 24 weeks of unsupervised home-based exercises. The app works by tracking completion of weekly exercise sessions, providing regular messages to facilitate weekly exercise and providing personalised messages to help overcome individual barriers to exercise participation. The two primary outcomes are i) self-reported physical function; and ii) number of days strengthening exercises were performed (previous fortnight), with a primary endpoint of 26 weeks and a secondary endpoint of 14 weeks. Secondary outcomes include knee pain severity; knee-related quality of life; global change; exercise program satisfaction; exercise self-efficacy; physical activity; sport and recreation function; another measure of exercise adherence; and willingness to undergo joint replacement. Process measures are also included.

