We recently developed a theory-informed mobile app called ‘My Exercise Messages’ that is available to consumers for free in the Apple App Store and Google Play. The app was adapted from our effective short message service (SMS) program that delivers personalised behaviour change messages to overcome barriers to exercise participation in people with knee OA [27]. Our research has shown that the SMS program of behaviour change messages improved adherence to unsupervised home exercise over 24 weeks in people with knee OA and obesity compared to people who received no SMS messages [28]. We have also shown that the SMS program, in combination with unsupervised web-based exercise, improved pain and function at 24-weeks in people with knee OA [29]. People with knee OA who used the SMS program found that the behaviour change messages to encourage exercise participation instilled a sense of support and accountability [30]. As scalable implementation of a behaviour change SMS program is challenging, we re-packaged the behaviour change messages into a mobile app, to permit rapid delivery at scale free of charge to the consumer. A mobile app also allowed inclusion of additional behaviour change techniques that were not amenable to SMS delivery, such as a graphical display for monitoring exercise adherence.

The primary aims of the current randomised controlled trial (RCT) are to determine if the ‘My Exercise Messages’ app confers any benefits after two consultations with a physiotherapist for prescription of a home strengthening program on:i)physical function and/or;ii)home exercise performance (exercise adherence) at 26 weeks.

Secondary aims are to:i)determine if the app confers benefits on physical function and home exercise performance (exercise adherence) at 14 weeks;ii)determine if the app confers any benefits on other clinical outcomes (knee pain severity; knee-related quality of life; global change; exercise program satisfaction; exercise self-efficacy; physical activity; sport and recreation function; another measure of exercise adherence; and willingness to undergo joint replacement) at 26 weeks;iii)determine engagement with, and usefulness of, the app using a range of process measures; andiv)explore potential moderators of the app’s effect on the clinical primary outcome (function).

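### Alpha is divided as a fixed 0.025 per primary outcome with no recycling; Holm would recover power for the joint claim at the same N and the same 5% family-wise error

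*Protocol article*

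**What the plan says.** The article's Sample size calculations section sizes the trial on adherence, "with 80% power and an alpha of 0.025", and explains the level as "an alpha of 0.025 (alpha of 0.05 split between the two primary outcomes". The same level is used for WOMAC function: "a baseline to 26-week correlation of 0.5 [28], an alpha of 0.025 and 15% attrition [28". These are the only statements about multiplicity between the two primary outcomes.

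The Statistical analysis plan section describes the models but gives no significance threshold and no multiplicity rule for the primary outcomes. It refers to a SAP to be written and published before analysis and while blind. The primary aims, at the end of the Background, ask whether the app benefits "physical function and/or;ii)home exercise performance (exercise adherence) at 26 weeks". Either outcome can therefore support a claim by itself.

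**The concern.** A fixed split tests each outcome at 0.025 and makes no use of the other's result. Holm tests the smaller p-value at 0.025 and, if that succeeds, the larger at 0.05. It rejects everything the split rejects and sometimes more, controls family-wise error strongly at 5%, and needs no ordering of the outcomes and no assumption about their correlation.

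The difference shows when one outcome is clearly positive and the other has p between 0.025 and 0.05. With p = 0.001 for adherence and p = 0.04 for function, the split gives a negative result on the clinical primary outcome, while Holm gives two positive results. This matters here because the trial's rationale is that better adherence leads to better function, so both effects being real is the scenario the investigators expect. The claim that the app improves both outcomes is the one that loses most power under the split.

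**Working it through.** **Inputs from Sample size calculations.** Adherence: "minimum important difference of 1.2 sessions in the adherence primary outcome", "assuming a between-participant SD of 2.4 [27] and 15% attrition [28". Function: "This sample size ensures more than 80% power to detect the minimal important difference on the clinical primary outcome of 6 units in change", SD 12, baseline to 26-week correlation 0.5. Alpha 0.025 each; 91 per arm randomised.

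**Assumptions.** Sidedness is not stated (the Abstract says only "This is a two-arm, pragmatic, superiority randomised trial"); I take two-sided tests, which reproduce N. The correlation between the two test statistics is not given; I use 0 to 0.5.

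**Reproducing N.** With d = 1.2/2.4 = 0.5, n per arm = 2(z₀.₉₈₇₅ + z₀.₈₀)²/d² = 2(2.241 + 0.842)²/0.25 = 76.04, so 77. Then 77/0.85 = 90.6, so 91 per arm and 182 in total, as stated.

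**Expected z-statistics at 77 completers per arm.** The multiplier is √(77/2) = 6.205.
- Adherence: 0.5 × 6.205 = 3.102.
- Function, baseline-adjusted as the analysis section plans: SD = 12√(1 − 0.5²) = 10.39, so (6/10.39) × 6.205 = 3.582.
- Function as an unadjusted change score: SD = 12√(2(1 − 0.5)) = 12, so 3.102.

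**Power of each test alone.** The critical values are 2.241 (alpha 0.025) and 1.960 (alpha 0.05).
- Adherence: 80.5% at 0.025, 87.3% at 0.05.
- Function (SD 10.39): 91.0% at 0.025, 94.8% at 0.05.

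**Hand check at correlation 0, both effects real.**
- Split, both significant: 0.8054 × 0.9100 = 0.733.
- Holm, both significant (both p ≤ 0.05 and at least one ≤ 0.025): 0.8734 × 0.9100 + 0.8054 × 0.9476 − 0.8054 × 0.9100 = 0.825.
- Holm, adherence: 0.8054 + (0.8734 − 0.8054) × 0.9100 = 0.867.
- Holm, function: 0.9100 + (0.9476 − 0.9100) × 0.8054 = 0.940.

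**Correlation 0 to 0.5 (bivariate normal), both effects real.**

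| Power | Fixed split | Holm |
|---|---|---|
| Adherence | 80.5% | 86.2–86.7% |
| Function (SD 10.39) | 91.0% | 93.1–94.0% |
| Both significant | 73.3–76.2% | 82.5–84.0% |
| At least one significant | 95.3–98.3% | the same |

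With a function SD of 12, power for both rises from 64.9–69.5% to 75.8–78.5%, and each outcome from 80.5% to 85.0–86.0%.

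**Only one effect real (correlation 0.3).** Power for the real effect barely moves: adherence 80.5% to 80.7%, function 91.0% to 91.1%. The chance of a false claim on the outcome without an effect rises from 2.5% to about 4.4–4.7%, still below 5%.

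**Neither effect real.** Family-wise error is the same under both procedures: 4.9% at correlation 0, falling to 4.7% at 0.5.

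**The case against.** A reader might infer that the protocol commits to a rule under which each outcome must reach p < 0.025 whatever the other shows. The document does not say so. The split appears only as a planning alpha, and the analysis section states no threshold. Sizing each outcome at 0.025 is also how one would plan a Holm analysis, whose first step is at 0.025. The unseen SAP could specify Holm without contradicting the sample size. This objection stands, and the point is therefore conditional on the analysis following the split.

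A reader might also infer that the split or the sample size is wrong. Neither is. The split controls family-wise error at 5%, N reproduces exactly, and the stated power targets are met.

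The aims are worded as either or both, and power for at least one success is identical under the two procedures. The gain lies only in what can be claimed for the second outcome, and only when both effects are real. That stands too, though both effects being real is what the trial's rationale expects.

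Finally, a fixed split pairs each test with a matching 97.5% interval. Under Holm an outcome with p = 0.04 can be declared significant while its 97.5% interval includes zero. Preferring aligned intervals is defensible. It is a reporting cost to weigh against the power gained, not a reason to leave the rule unstated.

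**Conclusion.** The point holds as an efficiency improvement. The protocol's only multiplicity statement is a fixed 0.025/0.025 split, and nothing in it recycles alpha. If the analysis follows that split, Holm would raise power for the joint claim by about 8 to 9 points (about 9 to 11 if the function SD is 12), adherence by about 6 points and function by about 2 to 3, without changing N or the 5% family-wise bound.

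These figures rest on both planned effects being real, the article's SDs and attrition, two-sided tests and an assumed correlation of 0 to 0.5. If only one effect is real, the gain is about 0.2 points at most. The document does not support calling the plan erroneous or saying that it has ruled out a step-down test.

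**What to change.** Before unblinding, add one sentence to the SAP: the two primary outcomes at 26 weeks are tested by Holm, the smaller p-value against 0.025 and, if that is significant, the larger against 0.05. If the SAP already says this, confirm it. If the fixed split is kept on purpose, for instance to keep tests and intervals aligned, say so.

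Report 97.5% intervals for both outcomes with 95% intervals alongside, and state that neither maps one-to-one to the step-down decision. N stays at 182, and no new participants or data are needed. The cost is that sentence and the looser link between intervals and decisions. The change must be made while the analysts are blind to be credible, and the article's own timetable for the SAP allows that.

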### Statistical analysis plan

A biostatistician will analyse data while blind to group details. A Statistical Analysis Plan will be written and published on our research centre’s website prior to data analysis commencing and while blind to group allocation. Main between group comparative analyses will be based on intention-to-treat. Multiple imputation will occur if a primary outcome has more than 5% of data missing at 26 weeks. For the physical function primary outcome, differences in mean change (follow-up minus baseline) in function will be compared across groups via a mixed-effects linear regression model, adjusted for baseline values and the stratifying variable (physiotherapist). Terms for time and group by time interaction will be included as fixed effects, with random effects for participants and physiotherapists. A similar mixed-effects linear regression model will be used for the adherence primary outcome, except, as there is no baseline score, there will be no adjustment for baseline values and the outcome will be follow-up score. For secondary continuous outcomes, differences in mean change (follow-up minus baseline) will be compared between-groups using linear regression modelling adjusted for the outcome at baseline, and the stratifying variable. As there is no baseline score for the secondary continuous outcome EARS, the outcome measure is EARS score at 26-weeks and there will be no adjustment for baseline values. The proportion of participants in each group that show an improvement that reaches or exceeds the minimum clinically important difference in average walking pain (≥ 1.8 NRS units [56]) and physical function (≥ 6 WOMAC units [55]) will be calculated. For these and other binary outcomes, groups will be compared using risk differences and risk ratios, calculated from logistic regression models adjusted for the outcome at baseline (where available) and the stratifying variable of physiotherapist and fitted using generalised estimating equations.

We will explore potential treatment effect moderators on change in the physical function primary outcome at 26 weeks, based on the following a priori hypotheses:a. Baseline beliefs about exercise

Hypothesis- Participants who think that exercise is less effective for managing knee OA at baseline will report less improvement in physical function with the exercise plus app intervention, compared to those believing exercise is more effective (relative to the exercise group).b. Baseline confidence using technology

Hypothesis- Participants who are less confident using technology at baseline will report less improvement in physical function with the exercise plus app intervention, compared to participants with greater confidence (relative to the exercise group).

Interaction terms between randomised group and these variables will be included in linear regression models for the physical function primary outcome at 26 weeks, for each potential effect modifier separately.

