### Secondary outcomes

A range of secondary outcomes are being collected at baseline and 26 weeks (unless otherwise indicated). For continuous secondary outcome measures (excluding the Exercise Adherence Rating Scale (EARS), see below), change scores will be calculated using data from baseline and 26 weeks.i)*Knee pain during walking*Average pain on walking (over the prior week) is measured with an 11-point numerical rating scale that has terminal descriptors of ‘no pain’ (score = 0) and ‘worst pain possible’ (score = 10).ii)*Sport and recreation function*The Knee Injury and Osteoarthritis Outcome Score (KOOS) [49] sport and recreational activities subscale measures function in sports and recreational activities. It comprises five questions ascertaining function with sport and recreational activities over the last week, with 5-point Likert response options ranging from ‘none’ to ‘extreme’. Total score ranges from 0 to 100, with lower scores indicating more difficulty with sports and recreational activities.iii)*Knee-related quality of life*The KOOS [49] quality of life subscale measures knee-related quality of life. It asks four questions about knee-related quality of life over the previous week, with 5-point Likert response options. Total score ranges from 0 to 100, with lower scores indicating poorer quality of life.iv)*Physical activity*Physical activity over the prior week is measured via the Physical Activity Scale for the Elderly (PASE) [50]. It comprises 10 questions about frequency and duration of recreational, household and occupational physical activity over the prior 7 days. Total scores range from 0 to 793 and higher scores are indicative of more physical activity.v)*Exercise self-efficacy*The Self-Efficacy for Exercise Scale [51] measures self-efficacy expectations about ability to continue exercising in the face of perceived barriers. This 9-item tool has scores which range from 0 to 90, with higher scores indicating better exercise self-efficacy.vi)*Participant-perceived global changes*At 26 weeks, participants rate their global change from baseline in i) knee pain, ii) physical function, and iii) their knee overall, via individual 7-point Likert scales (ranging from “much worse/less” to “much better/more”). On each scale, participants who are moderately better or much better will be classed as improved and the rest as not improved.vii)*Satisfaction with exercise program (including the mobile app, if applicable)*At 26 weeks, satisfaction with the entire exercise program (including the mobile app for those who were randomised to receive it) is rated with a 7-point Likert scale (ranging from “extremely unsatisfied” to “extremely satisfied”). Participants who are moderately satisfied or extremely satisfied will be classed as satisfied and the rest as not satisfied.viii)*Exercise Adherence Rating Scale (EARS)*A secondary measure of exercise adherence is included (in addition to the primary adherence measure). At 26 weeks, participants rate their adherence to their prescribed home strengthening exercises using Section B of the EARS [52]. This has six items and each is scored with a 5-point scale (terminal descriptors of ‘strongly agree’ to ‘strongly disagree’). The total score ranges from 0 to 24, with higher scores indicating better adherence.ix)*Willingness to undergo knee joint replacement*

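### The adherence co-primary sets the sample size with no power in reserve, yet its model has no prognostic baseline covariate, although plausible predictors are measured before randomisation

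*Protocol article*

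**What the plan says.** All references are to the protocol article.

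- **Sample size calculations.** The trial is sized on adherence: "A sample of 182 (91 per arm) is necessary", at "with 80% power and an alpha of 0.025". The target difference is 1.2 sessions, the SD 2.4 and attrition 15%. WOMAC function is said to have more than 80% power at the same size, using a baseline correlation of 0.5.
- **Statistical analysis plan, function.** The mixed model adjusts for the baseline value and for physiotherapist.
- **Statistical analysis plan, adherence.** The model is described as similar, except that "as there is no baseline score, there will be no adjustment for baseline values and the outcome will be follow-up score".
- **Statistical analysis plan, EARS.** Likewise, "the outcome measure is EARS score at 26-weeks and there will be no adjustment for baseline values".
- **Secondary outcomes.** The Self-Efficacy for Exercise Scale (0 to 90), collected at baseline and 26 weeks, "measures self-efficacy expectations about ability to continue exercising in the face of perceived barriers".
- **Other measures.** All participants rate at baseline, on four levels, how effective they think exercise is for knee osteoarthritis.
- **Randomisation, blinding and allocation concealment.** The baseline questionnaire is completed before enrolment, and allocation is revealed after it.

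**The concern.** The plan gives a true premise: there is no baseline adherence score. Adherence is asked only at 14 and 26 weeks and concerns a programme not yet prescribed at baseline. People doing knee strengthening in the previous six months are excluded in any case. But the premise removes only one covariate, the outcome's own baseline. It does not show that other pre-randomisation variables have nothing to offer.

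The article itself points to candidates. Its Background lists beliefs about capability for exercise, and about what exercise leads to, among the barriers to taking part. The self-efficacy scale addresses the first and the effectiveness question the second, and both are collected in both arms before allocation.

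What is at stake is precision on the outcome with least room to spare. Function, whose power may be appreciably higher, gets a prognostic covariate; adherence, which determined the sample size, gets none.

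**Working it through.** **Inputs from Sample size calculations.** Difference 1.2, SD 2.4 (standardised effect 1.2/2.4 = 0.5), power 80%, attrition 15%, and "an alpha of 0.025 (alpha of 0.05 split between the two primary outcomes". Sidedness is not stated. Two-sided is used because it reproduces the stated total; one-sided gives 63 per arm, or 75 after attrition (150 in total).

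**Step 1: reproduce the plan's figure.** By the normal approximation, n per arm = 2(z₀.₉₈₇₅ + z₀.₈₀)² / 0.5² = 2(2.241 + 0.842)² / 0.25 ≈ 76.0, rounded up to 77. Inflated for attrition, 77/0.85 = 90.6, rounded up to 91 per arm and 182 in total. This matches exactly.

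**Step 2: unadjusted power at that size.** Expected completers per arm are 91 × 0.85 = 77.35. Power is 80.7% by the normal approximation and 80.0% by the noncentral t distribution. The planned power is met with nothing over.

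**Step 3: function, for comparison.** With SD 12 and correlation 0.5 used through baseline adjustment, the residual SD is 12 × √(1 − 0.25) = 10.39. Power for 6 units is then about 91%. If 12 is instead taken as the SD of change with no further gain from adjustment, power is the same as for adherence (80.7% normal, 80.0% noncentral t).

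**Step 4: effect of a prognostic covariate on adherence.** The residual SD becomes 2.4 × √(1 − r²), where r is the correlation of the covariate (or the multiple correlation of the set) with 26-week adherence. The article gives no r, so a range is assumed. Power is by noncentral t with 77.35 per arm and two-sided alpha 0.025. Total N is for 80% power by the normal approximation, with 15% attrition.

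| Assumed r | Residual SD | Power | Gain over r = 0 (points) | Total N for 80% power |
|---|---|---|---|---|
| 0 | 2.40 | 80.0% | 0 | 182 |
| 0.1 | 2.39 | 80.5% | about 0.4 | 180 |
| 0.2 | 2.35 | 81.8% | about 2 | 172 |
| 0.3 | 2.29 | 83.9% | about 4 | 166 |
| 0.4 | 2.20 | 86.9% | about 7 | 152 |

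**Step 5: cost.** Continuous self-efficacy uses one degree of freedom. Belief, with four levels, uses one if entered as linear or three if categorical. That is at most four, against about 2 × 77.35 − 2 ≈ 153 in the two-group comparison. The table does not deduct them.

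**The case against.** The strongest reply is that nothing here is an error. The unadjusted comparison is valid under randomisation. It agrees with the sample size calculation, which assumes no covariate gain and reaches its 80%. Chance imbalance in self-efficacy is already reflected in the standard error. Adjusting only for an outcome's own baseline and the stratifying factor is also a simple rule applied consistently across outcomes. Finally, a separate SAP is promised before analysis and while blinded, and naming further covariates there would contradict nothing. All of this stands, and it limits the point to an avoidable loss of precision.

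Four stronger readings may tempt a reader, and the article does not support them:

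- **That the adherence model has no covariate at all.** It is described as similar to the function model, with only the baseline value dropped and the follow-up score as outcome, so physiotherapist remains.
- **That strong predictors are being ignored.** No correlation between any baseline variable and adherence is reported. The outcome is also bounded from 0 to six or more days, which may weaken linear prediction.
- **That the analysis is biased or underpowered.** It is neither on the stated assumptions.
- **That the responder analyses omit baseline severity.** Binary outcomes are adjusted for their baseline where there is one. For responder status this can reasonably be read as the baseline pain or WOMAC score, so the wording is ambiguous rather than deficient.

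What the reply does not remove is that the article is not silent: it fixes no baseline adjustment for adherence and EARS, for a reason that covers only the same-scale score.

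**Conclusion.** The point holds as a low-cost improvement, not as a correction of an invalid analysis. Adherence sets the sample size and has 80.0% power with no margin. Its model contains physiotherapist but no prognostic baseline variable, although two plausible ones are already in hand.

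The size of the benefit is uncertain. It ranges from about 0.4 points of power at r = 0.1 to about 7 at r = 0.4, and is nil at r = 0. These figures rest on the protocol's SD, difference and attrition, a two-sided alpha of 0.025, a simple two-group comparison at 26 weeks and an assumed r. The SAP is not shown; if it already names such covariates, the point is settled there.

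**What to change.** Before unblinding, state in the SAP that the adherence mixed model and the EARS regression include baseline exercise self-efficacy (continuous) as a fixed covariate alongside physiotherapist. Belief in exercise effectiveness may be added, with its coding (linear or categorical) stated. Replace the present reasoning with a sentence saying that the outcome's own baseline is unavailable and that these variables are used instead. The choice must be fixed in advance, because a covariate added after unblinding would look selected.

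As a separate minor clarification, state that the walking-pain and physical-function responder models adjust for the continuous baseline NRS or WOMAC score.

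The cost is analysis wording and a few degrees of freedom. No new data are needed, and little missing covariate data is expected because the baseline questionnaire precedes enrolment.
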